# Copen-SCALE: scaling-up an effective intervention to childcare institutions in Copenhagen – a stepped wedge type II hybrid effectiveness-implementation trial. A study protocol

**DOI:** 10.1186/s12889-025-24463-9

**Published:** 2025-10-09

**Keywords:** Childcare worker, Occupational health, Implementation, Scale-up, Incomplete stepped wedged cluster trial, Musculoskeletal pain, Sickness absence

## Abstract

**Background:**

This study protocol describes the evaluation of the scale-up of an effective intervention to potentially all 350 childcare institutions in Copenhagen. This project represents a unique opportunity previously unseen in occupational health and safety – namely the scale-up of an effective workplace intervention (TOY) to hundreds of workplaces. The aim of the project is to evaluate the scale-up of the TOY intervention, titled “Copen-SCALE.”

**Methods:**

The study is a 4-year type II hybrid stepped-wedge trial that will evaluate the effectiveness, cost-effectiveness, and implementation of an intervention across up to 350 childcare institutions in Copenhagen Municipality. The original TOY intervention included three participatory ergonomic workshops at childcare institutions, facilitated by external ergonomic consultants. The intervention had high feasibility and demonstrated a significant reduction in pain-related sickness absence among the childcare workers. Copen-SCALE’s target population now includes childcare workers in both day nurseries (ages 0–3) and pre-schools (ages 3–6), expanding beyond the original TOY RCT trial group. Moreover, there has been further development of the intervention by including best practices and research findings to the TOY concept, leading to the development of Copen-SCALE. Copen-SCALE includes four evidence-based components: child self-reliance, ergonomics, pain management education, and health-promoting activities. Copen-SCALE aims to include up to eighty-seven childcare institutions each year from 2024 to the end of 2027. Mixed methods will be employed to investigate effectiveness, cost-effectiveness, adaptation, and implementation of Copen-SCALE.

**Discussion:**

Scaling up effective interventions is crucial for achieving widespread benefits. Yet, this is underexplored in occupational health. The TOY intervention, being cost-effective and scalable, has the potential to contribute with valuable evidence, informing policies to enhance childcare workers’ health, well-being, and work environment. We anticipate that the findings from this project will inform wider dissemination of the intervention to childcare workers in more municipalities in Denmark.

**Trial registration:**

The study was prospectively registered in a clinical trial register (ISRCTN14831585). Registered 04 January 2024, ISRCTN - ISRCTN14831585.

**Supplementary information:**

The online version contains supplementary material available at 10.1186/s12889-025-24463-9.

## Background

Childcare serves as a fundamental social service and allows parents to participate in employment, education, and training, all the while ensuring the well-being and growth of their children in a stable and nurturing setting. The profession of childcare is however facing a labor shortage globally [1]. Danish childcare workers report high prevalence of musculoskeletal pain (38%), compromised mental well-being, and as much as 14 days annual sickness absence [2, 3]. The research literature points towards high physical and psychosocial work demands, musculoskeletal pain, and poor mental health and stress as main contributors to the high rates of sick leave and turnover among childcare workers [4, 5]. Consequently, there is a compelling need to ensure the vitality of childcare workers, enhancing their ability to care for children for more years.

Musculoskeletal pain is one of the biggest burdens of disease globally affecting approximately 1.71 billion people corresponding to about 149 million years lived with disability [6]. In Denmark, musculoskeletal pain represents the predominant cause for visits to general practitioners, hospital admissions, premature workforce attrition and sick leave episodes [7]. The associated annual costs incurred by the healthcare system of musculoskeletal pain are estimated to be 12 billion DKK, with an additional productivity loss of 40 billion DKK [7]. Demanding physical tasks at work contribute to a noteworthy proportion of low back pain (25%) and absenteeism (up to 40%) [8, 9]. Therefore, musculoskeletal pain puts a substantial toll on workplaces, highlighting the compelling rationale for workplaces to prevent musculoskeletal pain.

In the years 2018–2019, we conducted a randomized controlled intervention involving 190 childcare workers across sixteen childcare institutions in Copenhagen. The objective was to improve the capability of childcare workers in promoting self-reliance and learning among nursery children, incorporating ergonomic considerations, especially in physically demanding situations. This initiative was known as the TOY project [10]. The intervention had high feasibility and demonstrated a significant reduction in pain-related sickness absence among the childcare workers [11]. Moreover, the intervention had low implementation costs, and the return-on-investment of the intervention was 63%, indicating a monetary benefit for the childcare institutions [12].

Because of these findings, the Children and Youth Administration in Copenhagen Municipality opted to expand the TOY intervention. The scale-up initiative is set to encompass all 350 childcare institutions within the municipal area, with implementation scheduled to commence from the beginning of 2024 and extend through 2027. Participation will be voluntary. The TOY intervention was fundamentally a collaborative effort involving the participating workplaces as well as occupational health and safety representatives within the municipality (ergonomic consultants), thus ensuring its practical viability and efficacy. Importantly, the intervention was implemented under realistic conditions, involving the training of local implementers for intervention delivery.

Hence, the TOY intervention aligns with the concept of scalability, defined as “*the capacity of a health intervention proven efficacious within controlled settings or on a small scale to be extended into real-world scenarios*,* encompassing a more substantial portion of the eligible population while upholding its effectiveness*” [13]. These findings support that the TOY intervention is sufficiently cost-effective for scale-up to childcare institutions.

The original TOY intervention consisted of three participatory ergonomic workshops conducted at each childcare institution during regular staff meetings facilitated by an ergonomic consultant (an occupational therapist or a physiotherapist) from the Working Environment Consultancy Copenhagen.

Participants were briefed on the intervention’s primary focus, integrating participatory ergonomic action plans into their core tasks. The intervention, guided by a six-step participatory ergonomics framework inspired by Haines and colleagues [14], began with pain mapping and risk identification in the first workshop. Working teams then created and implemented action plans based on their findings. The second workshop involved evaluating the initial solutions and creating new action plans, while the third workshop assessed the new plans and discussed how to sustain changes [15]. Between workshops, childcare workers implemented 85% of suggested solutions during their working day [16].

Scaling up an intervention requires adaptations. In the process of scaling up TOY, a first adaptation has already been required. This is that the Copenhagen municipality has decided to expand the target population from childcare workers in day nurseries for children aged 0–3 (population in the TOY RCT trial) [10], to also include childcare workers in pre-schools for children aged 3–6 in Copen-SCALE. Moreover, since finalizing TOY in 2019, the Working Environment Consultancy Copenhagen have collaborated on other research projects and have added new best practices and research findings to the TOY concept, leading to the development of Copen-SCALE. In addition to the elements from TOY (ergonomics and children’s self-reliance and motor skills), Copen-SCALE also includes dimensions focusing on educating workers how to prevent and handle pain [17], as well as incorporating more health-promoting physical activities in their daily work routine [18]. Copen-SCALE thus consists of four evidence-based areas of intervention: (1) children’s self-reliance and motor skills, (2) ergonomics, (3) education in prevention and handling pain, and (4) health-promoting physical activity.

This study aims to evaluate the effectiveness, cost-effectiveness, implementation, and adaptation of the Copen-SCALE intervention in up to 350 childcare institutions within Copenhagen municipality. This will be completed in a type II hybrid effectiveness-implementation trial with several studies: The first two studies, an effectiveness evaluation and economic evaluation, will be conducted utilizing an incomplete stepped-wedge controlled trial [19] with the primary outcome of pain-related sickness absence. The next study is an evaluation of the required adaptations to the TOY intervention to enable the scale-up. This evaluation will consider changes at the interventional level as well as the institutional level. The fourth study is an implementation evaluation focusing on the following outcomes: 1) acceptability, (2) adoption, (3) appropriateness, (4) cost, (5) feasibility, (6) fidelity, (7) penetration, and (8) sustainability.

We anticipate that the findings from this project will inform wider dissemination of the intervention to childcare workers in Denmark.

## Methods

### Data protection, ethical approvals, and trial registration

The National Research Center for the Working Environment has an institutional agreement with the Danish Data Protection Agency about procedures to treat confidential data (journal number 2015-41-4232). The Danish National Committee on Biomedical Research Ethics (the local ethics committee of Frederiksberg and Copenhagen) has reviewed the study description and determined that according to Danish law it is not necessary to seek formal approval (H-23049692). Written informed consent to participate in this study will be provided by the participants. Moreover, the study was prospectively registered in a clinical trial register (ISRCTN14831585). The study is reported according to The StaRI standard checklist [20].

### Setting and participants

All 350 childcare institutions in the municipality of Copenhagen are invited to be enrolled in Copen-SCALE. All childcare workers (~ 7.200) [21] in the 350 childcare institutions will be eligible for participation in the evaluation. Copen-SCALE is planned to have a duration of 4 years, including up to eighty-seven childcare institutions per year, beginning in January 2024 and ending ultimo 2027.

### The intervention

Copen-SCALE consists of four evidence-based areas of intervention: (1) children’s self-reliance and motor skills, (2) ergonomics, (3) education in prevention and handling pain, and (4) health-promoting physical activity. The intervention involves a structured 3-hour workshop with employees during working hours, cf. Figure 1. This workshop focuses on educating childcare workers about the intervention components while also encouraging them to identify specific work-related challenges they wish to address. Additionally, participants develop actionable plans to improve their work situations. Following the workshop, the intervention includes 2 to 3 visits by a consultant at the workplaces. During these visits, the consultant provides ongoing support and monitors the implementation of the intervention to ensure its effectiveness and sustainability.

**Fig. 1 Fig1:**
[figure not shown]
Intervention model for Copen-SCALE. Copen-SCALE consists of four evidence-based components. The intervention begins with a three-hour workshop during working hours, educating childcare workers in key areas within the four intervention components, and prompting them to identify work-related challenges and develop action plans. Subsequently, two to three consultant visits occur over a period of 3–6 months to provide ongoing support and monitor implementation for sustainability

### Implementation strategies

Copenhagen Municipality has chosen to scale up the adapted TOY intervention to all childcare institutions, giving rise to the Copen-SCALE initiative. The municipality has formulated a business plan, securing funding for delivery and implementation of the Copen-SCALE implementation over the forthcoming four years. The childcare institutions involved will receive compensation for the time dedicated to implementing the intervention. The intervention will be implemented over 6–8 months in each individual institution, and as in TOY, consultants from the Working Environment Consultancy Copenhagen will deliver the intervention in Copen-SCALE. The Working Environment Consultancy Copenhagen specializes in workplace ergonomics and has previous experience with workplace health and safety research projects.

## Effectiveness evaluation

### Study design

This is a 4-year prospective type II hybrid stepped-wedge controlled trial evaluating effectiveness and cost-effectiveness outcomes along with an implementation evaluation [22]. The gold standard for an intervention study is usually a randomized controlled trial (RCT). Randomization is not always feasible when conducting scale-up studies because of the dynamic context in which they occur [19, 23, 24]. Hence, this intervention utilizes a pragmatic stepped-wedge controlled trial design, a methodology that has exhibited success in prior workplace studies [10, 11, 25]. A stepped wedge controlled trial assesses an intervention rolled out in stages over multiple periods. There is considerable variety in the design and conduct of stepped wedge controlled trials. One modification is the incomplete cross-sectional stepped-wedge cluster-controlled trial, where not every cluster is measured at every time point (17). The incomplete cross-sectional stepped-wedge cluster-controlled trial fits well with the planned implementation of the 350 childcare institutions over the course of 4 years, equivalent to about forty-four institutions per sixth month intervention period. The clusters will be formed based on the preferences of childcare institutions, and not by randomization. Randomization was not possible due to the restrictions from the Copenhagen Municipality in how to implement the intervention. The non-randomization is a limitation, but we will adjust for potential confounders in the analyses (see later). The design is illustrated in Fig. 2. A cluster consists of the workplaces that begin the intervention within a given period (spring or autumn). The baseline measurements from clusters prior to implementing the intervention will function as controls for the previous cluster who has completed the intervention. Follow-up measurements (F) will then be compared to baseline measurements (B) and serve as a control (Fig. 2).

**Fig. 2 Fig2:**
[figure not shown]
The incomplete non-randomized stepped-wedge design. The institutions within each cluster made up by time periods (spring/autumn) will be measured before the intervention is implemented (at baseline = B) and then after 6–8 months (at follow-up = F). For practical reasons, the institutions within each cluster will start the intervention at different time points within the 6-month intervention period. When a cluster completes the intervention and has their follow-up measurement, the baseline measurement of the next cluster will function as a control

### Sample size

It is important to consider statistical power when designing an implementation study. As implementation research is aimed at system-level changes, the power of a given study depends on working units (e.g., childcare institutions) as opposed to individual employees. Therefore, traditional methods of sample size and power calculation are usually not applicable as they fail to consider clustering and the extended time-frames of implementation studies [26]. To address this complexity, we utilize a recommended tool, the Optimal Design with Empirical Information (OD+), for effectively planning and powering these complex study designs [27]. Considering a power of 80%, an alpha level of 0.05, and a reliability of 0.70, the required sample size for our study is determined to be seventy-four childcare institutions. Given that we have up to 350 eligible childcare institutions for participation, we believe that we will be able to fulfill the targeted number in our sample size calculation.

### Data collection

Data collection will primarily be distributed to the childcare workers through a weblink on AULA (A digital platform used by childcare institutions in Denmark for communication within the institution) that directs them to the electronic questionnaire (SurveyXact). Data will be collected for all childcare workers at baseline and after the intervention period (approximately 6–8 months). To ensure data integrity, a blind assessor will check each variable for *out of range* or *implausible values*. Once all data are checked, we will import the dataset in panel format, into RStudio.

To ensure data integrity, a blind assessor will check each variable for *out of range* or *implausible values*. Once all data are checked, we will import the dataset in panel format, into RStudio.

To describe the study population, we will collect data on the childcare workers including sociodemographic information (i.e., age, sex, and work-related factors such as job title, seniority, weekly working hours), work environment factors, and psychosocial work environment factors measured using questions from the Danish Psychosocial Questionnaire [28]. Moreover, information about each childcare institution (e.g., type of institution (public or private), number of units, and number of employees) will be collected from registers from the municipality.

### Effeciveness outcomes

With inspiration from Proctor et al., we have divided the outcomes into implementation outcomes (see later), organizational and individual outcomes [29]. Thus, the effectiveness outcomes are measured as organizational outcomes, individual outcomes (employees).

### Organizational outcomes

At the organizational level, we will use the workplace registrations for sickness absence (absenteism). Presenteism will be measured by questionnaire at the employee level [30, 31]. Together, this information will be used for the cost-effectiveness analysis from the perspective of the employer (described later).

### Individual outcomes

At the individual participant level, we will collect information from questionnaires using validated questions. The main focus will be pain-related sickness absence [32], musculoskeletal pain (location, duration and intensity) [33, 34], work-related pain interference [35], self-perceived physical activity literacy [36], fear avoidance [37], physical exertion and pain-related occupational health literacy [17].

### Effectiveness analysis

Evaluation of effectiveness of the intervention will be performed using multilevel analyses using pooled individual level data. Multilevel analyses take clustering of observations of workers within the same team into account [38]. All analyses will be performed according to the intention-to-treat principle, including all eligible participants without imputations because mixed models inherently account for missing values [39]. In this analysis, the intervention will be modeled as a fixed effect and participants will be entered in the model as a random effect nested in clusters to account for the cluster design. Time will be treated as a dummy-coded categorical variable, and we will examine group × time interactions to determine intervention effects. In addition, we will take into account the possible differences between the groups at baseline [40]. Moreover, we will adjust for possible confounders at both individual and organizational level due to the non-randomization.

The mixed model analysis requires assumptions about the data. These include independence of observations, normality, and heteroscedasticity. Moreover, we will also consider other distributions of data and use the most appropriate statistical model for the collected data. Missing data are assumed to be Missing at Random. Missing at Random describes the probability of a missing observation being independent of prior observations, but conditional on other observed values. Repeated measures analysis also assumes a correlation structure between the repeated measurements. The correlations can be fixed (structured model), decaying (autoregressive model) or unconstrained (unstructured model). We will check the correlations between the repeated assessments and use the appropriate correlations according to the best model fit (tested by likelihood ratio test) [38–40].

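### The analysis section assigns the intervention effect to group × time interactions, which do not carry the average effect in this design and conflict with the intervention term named just before

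*Protocol article*

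**What the plan says.** The Study design section describes an incomplete, non-randomized stepped wedge. A cluster is the set of workplaces that start in the same spring or autumn; I call it a wave. The rollout is "equivalent to about forty-four institutions per sixth month intervention period". Each wave is surveyed before the intervention (B) and again 6–8 months later (F). On the comparison the section says: "The baseline measurements from clusters prior to implementing the intervention will function as controls for the previous cluster who has completed the intervention". The legend of Fig. 2 repeats it: "When a cluster completes the intervention and has their follow-up measurement, the baseline measurement of the next cluster will function as a control". On allocation: "The clusters will be formed based on the preferences of childcare institutions, and not by randomization".

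The Effectiveness analysis section first enters the intervention as a fixed effect, with participants random and nested in clusters. The next sentence reads: "Time will be treated as a dummy-coded categorical variable, and we will examine group × time interactions to determine intervention effects". It then adds that "we will take into account the possible differences between the groups at baseline" and promises adjustment for individual and organizational confounders. It does not say whether group means wave or treated/untreated, whether time means B/F or calendar period, or in what form baseline differences enter the model.

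**The concern.** A group × time interaction estimates a treatment effect when one group stays untreated at both times: its change over time is subtracted from the treated group's change. This design has no such group. Every wave moves from untreated to treated, and the control for one wave's F is another wave's B at about the same date.

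An analyst who follows the interaction sentence literally could therefore report no intervention effect for a programme that works equally well in every wave. An analyst who follows the sentence before it would report a different quantity. The primary outcome, pain-related sickness absence, would then depend on which sentence is followed. The open wording on baseline differences adds a second risk, because one natural way of making that adjustment removes the effect from the model.

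**Working it through.** **Layout.** From Study design: 350 institutions over 4 years with two starts a year gives 350/8 = 43.75, which agrees with the stated figure of about 44. So there are 8 waves (k = 1…8). With B of wave k in half-year k and F in half-year k + 1, there are 9 half-years and 16 observed cells. The idealization to half-years is mine; the text describes the scheme, but the figure is not shown. Let x = 0 at B and x = 1 at F, t = half-year, and w = wave. In every cell

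x = t − w.

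**What the interaction measures.**

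| Group | Time | Result |
|---|---|---|
| Wave | B/F | All 7 interaction terms are exactly 0 for a common effect of 0, −1 or −5. They show only whether waves change by different amounts. |
| Wave | Calendar period | Main effects already use 8 + 9 − 1 = 16 degrees of freedom for 16 cells, so nothing is left for an interaction. |
| Treated/untreated, with main effect | Calendar period | 9 + 1 + 6 = 16 columns. The interactions are 0 for any common effect, and the effect is in the main term. |
| Treated/untreated, no main effect | Calendar period | 9 + 7 = 16 columns, rank 16. Each of the 7 terms is F of wave k minus B of wave k + 1 in one shared half-year. With a true effect of −1 each returns −1. |

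In the first row, falling back on the B/F main effect does not help, because it is effect plus secular trend: a true effect of −1 with a trend of 0.3 per half-year gives −1 + 0.3 = −0.7.

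**Adjusting for group.**

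- Period dummies + x: 10 columns, rank 10. The effect is estimable.
- Period dummies + x + fixed wave terms: 9 + 1 + 7 = 17 columns, rank 16. The effect is not estimable, because x = t − w: period effects j·θ and wave effects −k·θ reproduce any treatment effect θ exactly.
- Period dummies + x + one linear wave term: 11 columns, rank 10. The effect is again not estimable.
- Baseline outcome as covariate with only F as outcome: x = 1 in every row, so no contrast remains (by reasoning, not computed).
- Seven waves instead of eight give the same pattern for the wave terms: 9 of 9 without them, 14 of 15 with fixed waves.

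**Waves as random effects.** The fixed part keeps rank 10 of 10. Taking the residual SD of a cell mean as 1, the standard error of the effect is 0.535, 0.538, 0.565 and 0.738 for wave-to-residual variance ratios of 0, 0.1, 1 and 10. The ratios are assumed, since the article gives none.

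**What identification then rests on.** Suppose waves differ by d per successive wave after covariate adjustment. Then d·w = d·t − d·x. The period dummies absorb d·t, and −d goes to the intervention coefficient whatever the covariance weights. Check: d = 0.2 and a true effect of 0 gave −0.200 at variance ratios 0, 0.1 and 1.

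**One exception to aliasing.** With monthly calendar time and fixed institution effects, the effect is not estimable if the B–F gap is constant. If the gap varies over 6–8 months (assumed uniform; one simulated layout of 344 institutions), it is estimable, but with 1.72/172 ≈ 1/100 of the information of a before–after comparison.

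**The case against.** The strongest reply is that the sentence before the interaction already enters the intervention as a fixed effect, with clusters handled through random effects. Together with dummy-coded time this is essentially the model that works. That stands. A reader might infer that the primary analysis as written cannot estimate the effect at all; the article does not support this, because it also names an estimable term. The fault is that the next sentence assigns the effect elsewhere.

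A reader might also infer that no interaction could ever give the effect. That goes too far. A treated × period coding without a main effect returns the period-specific contrasts that Study design describes. But the article does not specify that coding, and it yields seven contrasts rather than one average effect.

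A third tempting reading is that adjusting for baseline differences makes the effect inestimable. That holds only for fixed or linear wave terms combined with categorical half-years. The article names neither these nor a baseline-outcome covariate, so the point is conditional.

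Finally, the article openly calls the lack of randomization a limitation and promises confounder adjustment. The −d bias applies only to what the covariates leave behind, and it affects the model recommended below just as much. It is therefore no evidence against the interaction sentence. Nor can it be turned into a false-positive rate, because the article gives no effect size, intraclass correlation or number of respondents per institution.

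**Conclusion.** The point holds as a stated inconsistency in how the main effectiveness result is defined. Under the three usual codings, the quantity said to determine the intervention effect is zero for a common effect or has no degrees of freedom. This is a rule stated wrongly, not a detail left to an analysis plan.

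Aliasing is exact but conditional on how baseline group differences are modelled. With random waves the effect is identified only by assuming that self-selected waves are comparable given covariates, with a bias of −d for a residual linear gradient of d per wave.

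These results assume half-year periods and the B/F scheme described in the text. They concern the linear predictor, so a change of outcome distribution, which the article allows, does not alter the aliasing.

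**What to change.** Replace the interaction sentence with text to this effect:

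> The intervention effect is the coefficient of a time-varying indicator (0 = baseline survey, 1 = follow-up survey) in a mixed model with calendar-period fixed effects, individual and organizational confounders, and random effects for wave, institution and participant. Interactions of this indicator with time are examined only for heterogeneity of the effect. Baseline differences between waves enter through covariates and random effects; neither fixed or linear wave terms nor the baseline outcome as a covariate are included.

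State beside it that the estimate assumes waves to be comparable given the covariates. Optionally, add a sensitivity table showing the estimate under assumed wave gradients; since the bias is −d, each row adds d to the estimate.

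The cost is a few sentences and, if wanted, one small table. No new data are needed and the survey schedule is unchanged.
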